## Abstract

**Background:**

Chronic pain is naturally aversive and often distressing for patients. Pain coping and self-regulatory skills have been shown to effectively reduce pain-related distress and other symptoms. In this trial, the primary goal is to pilot test the comparative efficacy of a single-session videoconference-delivered group pain education class to a waitlist control among patients with chronic pain.

**Methods:**

Our study is a randomized clinical trial pilot testing the superiority of our 2-h single-session videoconference-delivered group pain education class against a waitlist control. We will enroll 120 adult patients with mixed etiology chronic pain and randomize 1:1 to one of the two study arms. We hypothesize superiority for the pain education class for bolstering pain and symptom management. Team researchers masked to treatment assignment will assess the outcomes up to 3 months post-treatment.

**Discussion:**

This study aims to test the utility of a single-session videoconference-delivered group pain education class to improve self-regulation of pain and pain-related outcomes. Findings from our project have the potential to significantly reduce barriers to effective psychological treatment for pain, optimizing the delivery of increasingly vital online and remote-delivered intervention options.

**Trial registration:**

ClinicalTrials.govNCT04546685. Registered on 04 September 2020.

## Background

Chronic pain is a problem of considerable public health importance that is estimated to impact approximately 100 million Americans and cost society up to $635 billion annually [1]. Chronic pain is particularly challenging to treat given the limited efficacy of existing pharmacological treatments [2–4] and the multisession nature of current psychological treatments, which are difficult to integrate into healthcare settings and thereby perpetuating medical utilization, disparities, and disease. To date, the USA lacks scalable behavioral medicine for pain, underscoring the need for solutions that are accessible, low-cost, and low-burden.

Despite the documented benefits of cognitive behavioral therapy (CBT) for chronic pain [3, 5], it remains limited by multiple obstacles including treatment time, healthcare costs, travel burden, lack of services for patients in remote or rural areas, and lack of available trained therapists and services [6–9]. Given these barriers, as well as the rapidly expanding need for alternatives to face-to-face encounters due to the COVID-19 pandemic [10], there is an urgent need for brief online and remotely delivered psychological interventions. Online and remotely delivered interventions have been demonstrated to be effective in treating a variety of physical and mental health issues, with Internet-based CBT classified as a well-established treatment for depression, panic disorder, and social phobia [11]. Online CBT has also been found to be effective in treating psychological issues related to living with chronic illnesses, including irritable bowel syndrome, tinnitus, and chronic pain [12], with small-to-moderate reported effect sizes (*d* range 0.04 to 1.23, mean 0.60) in chronic pain [11]. Internet- and remote-delivered CBT is also effective in reducing pain catastrophizing and improving patient attitudes toward chronic pain [13]. Other online interventions for patients with pain include the use of compassionate mind training [14], social media-based online community intervention [15], pain self-management [16], and online hypnosis [17]. Although showing promising results, these were multisession interventions ranging from 20 days to 12 weeks, which can be costly, time-consuming, and burdensome for patients.

Increasingly, the field is trending toward a population health approach that uses ultra-brief and targeted behavioral treatments that have the greatest reach at the lowest cost and burden. Single-session interventions (SSIs) have shown promise and efficacy in diverse populations and health conditions such as serious mental illness [18], anxiety and conduct disorder in youth [19], acute insomnia [20], heavy alcohol consumption in college students [21], trauma and adversity [22, 23], postsurgical pain [24], and general chronic pain [25–29]. Several online SSIs have been conducted as well, with demonstrated feasibility and patient acceptance of online-delivered SSIs for multiple sclerosis pain [30], disordered gambling [31], and adolescent mental health [32–34]. Data suggest that SSIs are only slightly less effective than longer course treatments requiring up to 16 h of treatment time [29, 35]. Effective SSIs, especially if delivered digitally, would eliminate many barriers to care such as lack of available trained therapists, treatment cost and burden, and insurance limits.

Our team has developed and tested a 2-h skills-based SSI (“Empowered Relief”), which was shown to reduce pain-specific distress and improve self-regulation at a 4-week follow-up in a cohort of 57 mixed etiology chronic pain patients receiving treatment at a tertiary referral, multidisciplinary chronic pain clinic [25]. Importantly, in a 3-arm randomized controlled trial, Empowered Relief was non-inferior to an 8-week cognitive behavioral therapy and superior to a health education class for reducing pain-specific distress (i.e., catastrophizing) and improving multiple secondary outcomes at 3 months post-treatment in individuals with chronic low back pain. For the first time, the current study seeks to test the impact of a group-based single-session intervention “Empowered Relief” that is delivered online on bolstering pain and symptom management in adults with mixed etiology chronic pain. Participants who are randomized in the waitlist or usual care do not receive the study intervention and will be instructed to continue with the care they would normally receive as part of their ongoing clinical care. Upon completion of the 3-month study, participants in the waitlist will be invited to enroll in “Empowered Relief.”

## Specific aims

Our specific aim and three corresponding hypotheses are outlined below.
We will conduct a randomized controlled trial comparing the preliminary effects of a single-session videoconference-delivered pain education class compared to a waitlist control (i.e., usual care) condition.
Hypothesis 1: The single-session intervention (Empowered Relief (ER)) will lead to greater reductions in pain catastrophizing compared to a usual care condition.Hypothesis 2: ER will lead to greater reductions in pain bothersomeness and sleep disturbance compared to a usual care condition.Hypothesis 3: ER will lead to greater reductions in pain intensity, anxiety, depression, and physical function compared to a usual care condition.

## Methods/design

### Overview

We are piloting a randomized clinical trial in which individuals with a chronic pain condition are randomly assigned to one of two arms: a single-session videoconference-delivered group pain education class or a waitlist control (WLC) receiving usual care (Figs. 1 and 2). Participants will be followed for 3 months after treatment. Participants will be assessed via an online screening form, a phone screening, enrollment survey, 2-week follow-up, and at 1, 2, and 3 months post-treatment. Team statisticians blinded to participant treatment assignment will assess the outcomes 2 weeks after treatment and after 1, 2, and 3 months. The primary outcome is pain catastrophizing 1 month post-treatment. Secondary outcomes include reductions in pain bothersomeness and PROMIS sleep disturbance at 1 month post-treatment. Tertiary outcomes include reductions in pain intensity, PROMIS anxiety, PROMIS depression, and PROMIS physical function. The protocol for this trial has been approved by the Stanford Institutional Review Board (IRB). All participants will be required to give informed consent to a trained study team member prior to enrollment in the study.

**Fig. 1 Fig1:**
[figure not shown]
Flowchart of the trial protocol

**Fig. 2 Fig2:**
[figure not shown]
The schedule of enrollment, interventions, and assessments

### Study sample and setting

Participants for this trial will be recruited through targeted emails and advertisements at Stanford’s pain management clinics, in addition to the Stanford Systems Neuroscience and Pain Lab (SNAPL) database. All advertisements will direct interested individuals to an online screening form that assesses for initial eligibility. The study will enroll 120 adults (age >18 years) with a chronic non-cancer pain condition and who meet the study criteria (Table 1). The sample size accounts for expected attrition, and eligibility will be assessed by the research staff.

**Table 1 Tab1:** Inclusion criteria

Inclusion criteria	Rationale	Sources
Pain ≥3 months more than half the time	Study restricted to non-cancer chronic pain	A, TS
English fluency	Ability to complete study procedures	A, TS
Ability to adhere to and complete study protocols		A, TS
Males and females, 18+	Not including children	A, TS

*A*, automated data gathered from REDCap surveys; *TS*, telephone screening

### Inclusion and exclusion criteria

Tables 1 and 2 list the inclusion and exclusion criteria, respectively, as well as the rationale for each criterion and the sources where each criterion will be assessed. Additionally, we require that the participants be willing and available to participate in the full treatment session and able to respond to the enrollment survey (3–6 days before the class date) and post-treatment (2 weeks and 1, 2, and 3 months) follow-up questionnaires.

**Table 2 Tab2:** Exclusion criteria

Exclusion criteria	Rationale	Sources
Ongoing legal action or disability claim	Source of bias	A, TS
Previous participation in the ER class	Possible bias due to previous exposure to treatment	A, TS
Cognitive impairment, non-English speaking, or factors that would preclude comprehension of material and/or full participation in the study	Not able to complete study procedures	A, TS

*A*, automated data gathered from REDCap surveys; *TS*, telephone screening

### Recruitment procedures

Because the study intervention is group-based and delivered via videoconference, we are recruiting participants in 2–3 large cohorts consisting of 30 participants per class cohort (minimum of 20 participants, maximum of 30 participants per cohort) for both study arms.

Interested individuals deemed initially eligible by the online screening will be further screened over the phone. Eligible individuals will then be invited to enroll in the study and consented with a research staff over the phone, after which they provide an electronic signature to the consent form emailed to them. Participants are randomized following eligibility confirmation and informed consent procedures. Then, participants complete the enrollment survey, which includes information related to their chronic pain and psychosocial well-being.

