### Randomization

Enrolled participants will be randomized to one of two study arms: Empowered Relief (ER) and waitlist control (WLC; usual care). An automated program in REDCap will randomly assign a participant to a study arm when enrolled and will ensure blinded randomization, as well as equal numbers in both arms at the end of data collection.

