### Blinding

Participants cannot and will not be blinded to the study arm they are randomized to. A clinical psychologist who will be trained in the intervention and has no involvement in the data analysis will deliver the intervention. The study coordinator will be responsible for handling the randomization process through REDCap but will remain blinded to the randomization scheme. All data given to the statistician will be blinded. All research data will be kept separate from identifiers and linked using a participant number. Only the principal investigator will have access to the file linking names and participant numbers, and the file will be stored behind password-protected and fire-walled systems. The team will have access to the final unidentified dataset.

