#### Baseline (pre-treatment) assessment

Three to 6 days pre-treatment, patients will complete an online baseline survey including demographic information, pain condition and characteristics, pain bothersomeness, pain catastrophizing, and the PROMIS measures. Participants will not be asked to repeat demographic information again, but these measures will be identical to those assessed post-treatment.

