#### Secondary objectives

To test the secondary and tertiary aims that the ER class will have greater reductions in pain bothersomeness, sleep disruption, pain intensity, anxiety, depression, and physical function compared to WLC, our primary endpoint will be considered at 1 month post-treatment, and its within-subject difference from baseline will be calculated. The mean difference in the ER group will be compared against the WLC arm using the two-sample *t* test. Similarly, we will also compare the proportion of success rate, defined as ≥30% reduction in our outcomes for a clinically significant treatment response [52].

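### The self-reported baseline is collected after unblinded randomization, so change scores and 30% response rates are open to influence from knowledge of the arm

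*Protocol article*

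**What the plan says.** Under Recruitment procedures the order is explicit: "Participants are randomized following eligibility confirmation and informed consent procedures. Then, participants complete the enrollment survey". The Randomization section agrees that the REDCap program "will randomly assign a participant to a study arm when enrolled".

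The enrollment survey is the baseline assessment. The Inclusion and exclusion criteria section requires that participants be "able to respond to the enrollment survey (3–6 days before the class date"), and the Baseline (pre-treatment) assessment section uses the same window: "Three to 6 days pre-treatment, patients will complete an online baseline survey including demographic information". That section lists the outcome instruments among the contents: "pain bothersomeness, pain catastrophizing, and the PROMIS measures". No earlier measurement of these outcomes is described.

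On masking, the Blinding section says: "Participants cannot and will not be blinded to the study arm they are randomized to".

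On use of the baseline, the Secondary objectives section takes the 1-month endpoint for all secondary and tertiary outcomes and says "its within-subject difference from baseline will be calculated"; the arms are then compared by two-sample t test. Both analysis sections also compare the proportion with at least a 30% reduction, for the PCS and for the other outcomes. The primary t test is described only as a comparison of pain catastrophizing at 1 month, without saying whether the variable is the score or the change.

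**The concern.** Randomization makes the arms comparable on what was measured before it. A questionnaire filled in after allocation, by someone who may know the result, does not have that protection. A person told to wait three months may rate their distress differently from a person booked into a class within the week, and the difference could go either way. A person who loses interest on learning the allocation may never complete the survey.

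Two things are at stake. First, any between-arm difference in baseline reporting that is not also present at 1 month enters the change-score contrast and the 30% response rates as if it were a treatment effect, or hides one. Second, a randomized participant with no baseline has neither a change score nor a response status, and such losses need not be equal between arms. A baseline that was never collected before allocation cannot be recovered later by analysis.

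**Working it through.** **Inputs from the protocol article.** Randomization before survey (Recruitment procedures); no participant blinding (Blinding); change from baseline for secondary and tertiary outcomes (Secondary objectives); 30% reduction as response (Primary analyses and Secondary objectives); 120 enrolled, 116 completers, 58 per arm, 4% attrition, 80% power for a medium-large effect (Sample size and detectable differences).

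**Assumptions not in the article.** Two-sided 5% level; PCS SD 10–12; baseline/follow-up correlation r = 0.6 (range 0.5–0.7); a 2-point between-arm baseline shift. The shift has no source in the article and serves only to show scale.

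**Step 1: the plan's own figures.** 116 / 0.96 = 120.8, or 121, against 120 stated; 120 × 0.96 = 115.2, against 116. These agree to within rounding. With 58 per arm, 80% power is reached at a standardized difference of 0.525 (noncentral t), which fits the description medium-large. Nothing in the sample size is disputed here.

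**Step 2: how a shift enters.** Let δ be the between-arm shift in baseline reporting and k the fraction of it still present at 1 month.

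- Bias in the change-score contrast: (1 − k) × δ in size.
- Bias in the contrast of raw 1-month scores: k × δ.

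If the shift has gone by 1 month (k = 0), the change score takes all of it. If it persists fully (k = 1), it cancels in the change score and falls on the 1-month score. On direction: if waitlisted people report transiently more distress at baseline, the control arm appears to improve more and the bias runs against the class. If class participants report transiently more, it runs in favor of the class.

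**Step 3: size against the detectable difference, k = 0.** The SD of a change score is SD × √(2(1 − r)). At r = 0.6 this is SD × √0.8 = SD × 0.894.

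- SD 10: 0.525 × 0.894 × 10 = 4.7 points; 2 / 4.7 = 43%.
- SD 12: 0.525 × 0.894 × 12 = 5.6 points; 2 / 5.6 = 36%.

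**Step 4: false-positive risk on a change score, k = 0, no true effect.** The noncentrality is s / √(2(1 − r)) × √(58/2), where s is the shift in SD units. For s = 0.2 and r = 0.6: 0.2 / 0.894 × 5.385 = 1.20, giving a two-sided rejection rate of 22%.

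| Shift (SD) | r = 0.5 | r = 0.6 | r = 0.7 |
|---|---|---|---|
| 0.1 | 8% | 9% | 11% |
| 0.2 | 19% | 22% | 28% |

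**Step 5: 30% response, k = 0, no true effect.** Simulation with an assumed PCS baseline mean of 25, SD 10 and r = 0.6: raising the baseline in one arm by 2 points lifts its response rate from 17.6% to 22.4%, about 5 percentage points. The rise is also about 5 points at r = 0.5 and r = 0.7.

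**Step 6: missing baselines.** The plan allows for 120 − 116 = 4 losses in total. If, as an assumption, 10% of the 58 per arm had no baseline, 58 × 0.9 = 52 per arm would remain for the change analysis. Power at 0.525 SD would fall from 80.7% to 76.5% (normal approximation), apart from any selection effect.

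**The case against.** The strongest reply is that the article never says when participants learn their arm. Being unblinded is not the same as being told before the survey. The flowchart and the assessment schedule (Figs. 1 and 2) could not be read for this point and may show the order more finely. This stands as a limit: the bias is a risk created by the stated order, not a demonstrated event. It does not remove the point, because no sentence withholds the allocation. Scheduling class groups of 20–30 makes early notice plausible, although that is inference.

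A reader might infer that the primary result is compromised. The article does not support that. The Primary outcome measure section refers to scores at 1 month, and a t test on those scores would not use the baseline at all. Hypothesis 1 speaks of greater reductions, so a change score is possible, but the text leaves it open.

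A reader might also infer that a baseline shift always passes in full into the effect estimate. Step 2 shows that this is the extreme case: participants remain unblinded at follow-up, and a shift that persists would partly cancel.

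Nor do the documents show that intent-to-treat is broken. The Primary analyses section defines it as analysis by randomized group regardless of participation. Handling of missing baselines may be set out in an analysis plan not shown here, and no figure shows unequal loss. Finally, no covariate-adjusted analysis is planned, so its behavior with a post-randomization baseline is not at issue.

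What remains is the sequence itself. It is fixed in the text, not left for an analysis plan to settle.

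**Conclusion.** The point holds as a weakness in sequence. Randomization precedes an unblinded, self-reported baseline, and no safeguard is stated. All secondary and tertiary change-from-baseline tests and all 30% response comparisons, including the PCS response comparison listed under Primary analyses, depend on that baseline. The primary t test is exposed only if it uses change.

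The direction and size of any shift are unknown. Under the assumptions listed, a 2-point shift that has gone by 1 month would equal about 36–43% of the detectable change-score difference. That is a sensitivity illustration and not an estimate of bias in this trial. The case for acting is that prevention costs little and no later analysis can supply the missing pre-randomization measurement.

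**What to change.** Make submission of the baseline survey a precondition for running the REDCap randomization. Give all consented participants the class date, open the survey in the existing 3–6 day window, and randomize on submission. Alternatively, keep the present order but state that the allocation is not released to the participant until the survey is submitted. If scheduling needs earlier allocation, collect the PCS and the other outcome measures at consent, before randomization.

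For anyone already randomized before baseline, report baseline completion and baseline means by arm, and add a sensitivity analysis of the 1-month scores that does not use baseline. Note beside it that those scores are also unblinded self-reports, so the analysis avoids the baseline problem but not reporting bias at follow-up. State as well whether the primary t test uses the 1-month score or the change.

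The cost is a change of sequence in REDCap and in the recruitment text, and participants learn their arm only a few days before the class. The sample size stays at 120 and no measures are added.

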### Randomization

Enrolled participants will be randomized to one of two study arms: Empowered Relief (ER) and waitlist control (WLC; usual care). An automated program in REDCap will randomly assign a participant to a study arm when enrolled and will ensure blinded randomization, as well as equal numbers in both arms at the end of data collection.

### Blinding

Participants cannot and will not be blinded to the study arm they are randomized to. A clinical psychologist who will be trained in the intervention and has no involvement in the data analysis will deliver the intervention. The study coordinator will be responsible for handling the randomization process through REDCap but will remain blinded to the randomization scheme. All data given to the statistician will be blinded. All research data will be kept separate from identifiers and linked using a participant number. Only the principal investigator will have access to the file linking names and participant numbers, and the file will be stored behind password-protected and fire-walled systems. The team will have access to the final unidentified dataset.

### Study arms

Empowered Relief consists of a single-session 2-h videoconference-delivered group class. After the ER class, participants will receive home-based resources that facilitate ongoing self-regulation and pain self-management. Participants randomized to the waitlist control arm do not receive the study intervention and will be instructed to continue with the medical care they would normally receive. Upon completion of the 3-month study, participants in the waitlist control will be invited to enroll in ER.

